### Sampling technique

Purposive sampling of eligible clinic attendees will be used at each site until the zone allocation is achieved. To ensure national representation and account for regional variability: Equal allocation of participants was adopted, with 17 children per zone, resulting in a total of 102 participants. This pragmatic sample is intended to estimate prevalence estimates within this high-risk clinical cohort and support exploratory analyses of correlates.

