### Specific objectives

To estimate the prevalence of Fragile X full mutation and premutation among Nigerian children (1–18 years) with intellectual disability, autism spectrum disorder, or global developmental delay using molecular methods.To identify sociodemographic and clinical factors associated with Fragile X disorders in this population.To establish screening-to-care pathways, including result disclosure, genetic counselling, and referral for supportive interventions.To develop a context-appropriate model for integrating Fragile X screening into paediatric/developmental health services in Nigeria.

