### Data collection

A structured interviewer-administered proforma will capture – Child: age, sex, developmental history, clinical diagnosis, schooling status; Parent/guardian: age, education, occupation, household socioeconomic indicators, and family history.(S1 Appendix)Clinical assessment will include vitals, anthropometry, general examination and documentation of Fragile X-associated clinical features using established checklists [5,12].

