### Outcomes

The primary outcome is the proportion of participants with *FMR1* full mutation and/or premutation (those who test positive from the screening) in the selected cohort. Secondary outcomes include the distribution of CGG repeat sizes; the association of FMR1 expansion status with sociodemographic and clinical variables; the proportion of screen-positive families receiving counselling, referrals, and linkage to supportive interventions relevant to child mental health and developmental wellbeing; uptake of cascade testing offers; and building research capacity through mentoring early-career faculty members towards training in public health genetics. The study findings will be reported in accordance with the Strengthening the Reporting of Observational Studies in Epidemiology (STROBE) Statement.

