## Discussion

CHAMP-FX addresses a major Nigerian gap due to limited access to Fragile X molecular testing and an absence of epidemiologic data on Fragile X disorders. To our knowledge, this is the first multicentre protocol for Fragile X screening in Nigeria to implement a harmonised dried blood spot (DBS)-based workflow across the country’s six geopolitical zones. The study prioritises equity and capacity building while generating foundational data that may inform future Fragile X screening and service integration within paediatric and developmental health services. Given the 50% transmission risk from female carriers and the emergence of targeted therapeutic approaches, early identification of Fragile X syndrome may have important implications for genetic counselling, family screening and clinical management.

Operational challenges are anticipated, including DBS drying, storage and transport, laboratory turnaround time, and limited capacity for genetic counselling and follow-up. To address these challenges, the protocol incorporates standardised procedures, personnel training and defined referral pathways. The multicentre design also provides a platform for future studies, including more precise prevalence estimates and evaluation of models for integrating Fragile X screening into routine child health services.

This study has some limitations. The sample size was estimated using the best available local data, and participants will be recruited purposively from selected health facilities, which may limit the generalisability of the findings to the wider Nigerian population. Children who do not access formal health services may also be underrepresented. In addition, challenges related to counselling capacity and long-term follow-up may influence implementation across study sites. Despite these limitations, the study is expected to generate important preliminary evidence to inform future research, policy and service planning for Fragile X syndrome and premutation disorders in Nigeria.

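### Purposive choice among eligible clinic attendees, with no rule on who is approached, can bias the primary prevalence even for the clinic cohort, and it does not fit the claim of national representation.

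*Protocol article*

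**What the plan says.** The Sampling technique section of the Protocol article fixes the method: "Purposive sampling of eligible clinic attendees will be used at each site until the zone allocation is achieved". It does not say in what order, or by what rule, eligible children are invited. The same section gives the reason for equal quotas of 17 per zone as "To ensure national representation and account for regional variability", and then describes the target more narrowly: "This pragmatic sample is intended to estimate prevalence estimates within this high-risk clinical cohort and support exploratory analyses of correlates".

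The target also differs between sections. The first specific objective refers to Nigerian children aged 1–18 with any of the three diagnoses, whereas the Outcomes section says: "The primary outcome is the proportion of participants with *FMR1* full mutation and/or premutation (those who test positive from the screening) in the selected cohort".

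The Statistical analysis plan section lists the bias controls: recruitment in six zones, standard eligibility criteria and data collection, a central laboratory and prespecified analyses. The Discussion accepts that "participants will be recruited purposively from selected health facilities, which may limit the generalisability of the findings to the wider Nigerian population".

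**The concern.** Purposive sampling means that someone decides which eligible children enter. For a primary outcome that is a proportion, any link between that decision and Fragile X status passes straight into the estimate. None of the listed bias controls governs the choice among eligible attendees at a site.

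Two problems should be kept apart. The first is whether clinic attendees resemble affected children elsewhere in Nigeria, which the Discussion concedes they may not. The second is whether the 17 children chosen resemble the other eligible attendees of the same clinic. The second affects the estimate for the clinic cohort itself, and the article does not mention it. A 95% confidence interval describes random error only. Without a record of who was passed over, the analysis cannot repair the selection.

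The stated aim of ensuring national representation is also out of line with the Discussion. Seventeen judgement-selected children at one tertiary hospital per zone cannot ensure it. The results are meant to inform policy and service planning, so the description of what was sampled matters.

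**Working it through.** **Inputs.**
- Sample size and allocation: P = 0.023, Z = 1.96, d = 0.05, N = 28.9, 17 per zone, and 12 autism cases per 5 months at the coordinating site.
- Study period: recruitment February to September 2026, which is 8 months.
- Assumptions, not in the document: the selection ratio r, and the size of the eligible pool once intellectual disability and global developmental delay are counted.

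**The plan's own figures.**
- n = 1.96² × 0.023 × 0.977 / 0.05² = 34.5.
- nc = 34.5 / (1 + 34.5/28.9) = 15.7.
- 17 × 6 = 102.

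These reproduce, and the arithmetic is not in dispute. Expected positives in an unselected sample are 102 × 0.023 = 2.3.

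**Effect of selection when the pool is large.** Let r be the selection probability of a positive child divided by that of a negative child. The expected proportion is rP / (rP + 1 − P).

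| r (assumed) | Calculation | Expected proportion | Positives in 102 |
|---|---|---|---|
| 0.5 | 0.0115 / 0.9885 | 1.2% | 1.2 |
| 1 | 0.023 / 1.000 | 2.3% | 2.3 |
| 2 | 0.046 / 1.023 | 4.5% | 4.6 |
| 3 | 0.069 / 1.046 | 6.6% | 6.7 |

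**Ceiling set by the pool.** Upward bias cannot exceed the result of taking every positive child in the pool. The ceiling is P × pool / 17, taking the same pool at every site.

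| Pool per site in 8 months | Ceiling |
|---|---|
| 12/5 × 8 = 19.2 (autism only, coordinating site) | 0.023 × 19.2 / 17 = 2.6% |
| 2 × 19.2 = 38.4 (assumed) | 5.2% |
| 3 × 19.2 = 57.6 (assumed) | 7.8% |
| 4 × 19.2 = 76.8 (assumed) | 10.4% |

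The two tables must be read together. Reaching 4.5% needs a pool of at least 0.045 × 17 / 0.023 = 33 children per site. Reaching 6.6% needs 0.066 × 17 / 0.023 = 49. The ceiling limits upward bias only.

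**Comparison with random error.** The Wald 95% half-width at n = 102 is 1.96 × √(0.023 × 0.977 / 102) = 2.9 percentage points. The shift is 4.5 − 2.3 = 2.2 points at r = 2 and 6.6 − 2.3 = 4.3 points at r = 3. The second exceeds the half-width.

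**Feasibility of consecutive enrolment.** Autism attendance at the coordinating site is 12/5 = 2.4 per month, so 17 places fill in 17 / 2.4 = 7.1 months of the 8. On autism alone this requires 17 / 19.2 = 89% of cases to enrol. The other two diagnoses would ease this. Flow at the other five sites is not given.

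**The case against.** **Selection on Fragile X features is not documented.** A reader might infer that staff will pick children who look like Fragile X cases. The documents do not support that. The Data collection section does provide for "documentation of Fragile X-associated clinical features using established checklists", but as part of the assessment and not as a criterion for entry. No section says that staff are trained to select on such features. The sampling sentence could also mean no more than filling a quota from attendees who have a qualifying diagnosis. This objection stands: the text permits biased selection but does not describe it.

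**The bias may be small.** If the pool barely exceeds 17, there is little room to choose, and the 2.6% ceiling shows it. The same 19.2 cases cannot support both easy consecutive enrolment and a large upward bias. This also stands. However, eligibility covers two further diagnoses, and their numbers are not given.

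**Much is already disclosed.** The sample is called pragmatic, the target is narrowed to the clinical cohort, and purposive recruitment is named as a limitation. This stands in part, because the article is inconsistent rather than silent. The disclosure concerns generalisability and does not reach choice within the clinic.

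**Other readings go too far.**
- A reader might infer that siblings or children already known to be positive may enter. The Eligibility criteria section refers to Appendix A, which is not shown, so this cannot be judged.
- A reader might infer that the pooled proportion will be unweighted. The Statistical analysis plan section promises estimates with 95% confidence intervals and says nothing on weighting.
- A reader might infer that one extra positive child doubles the result. Going from 2 to 3 positives is a factor of 1.5; doubling takes two extra.

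**Conclusion.** The point holds as a design weakness of unknown size and direction. Purposive choice without an approach rule can bias the primary proportion even for the clinic cohort. Neither the listed bias controls nor the generalisability caveat addresses this, and the confidence interval will not reveal it.

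If 2.3% is the true clinic prevalence, an assumed selection ratio of 2 or 3 gives 4.5% or 6.6%, but only where the eligible pool is large enough. The upward limit runs from about 2.6%, for the autism cases at the coordinating site alone, to about 5% to 10% if the pool is two to four times larger. These figures rest on assumed values of r and pool size and are not a forecast. To say that the study will overestimate prevalence would go beyond the documents.

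Separately, and whatever the size of the bias, the aim of ensuring national representation conflicts with the Discussion and needs rewording.

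**What to change.** In the Sampling technique section, replace purposive sampling with consecutive enrolment. From a fixed start date, each site invites every eligible attendee until 17 are enrolled, irrespective of suspected Fragile X features or family history.

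Each site keeps a log of children eligible, approached, consented and declined, so that any departure from consecutive enrolment can be seen and reported.

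Replace the claim of national representation with a description such as attendees at six tertiary hospitals, one per zone, in line with the limitation in the Discussion.

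The change needs no larger sample and no new assay, only a wording change and a simple site log. Staff lose discretion over whom to invite, and enrolment may be slower at a low-volume site. Because attendance at the other five sites is not given, the time needed there should be checked before the rule is fixed. The log has to start with recruitment, since it cannot be reconstructed reliably afterwards.

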### Data collection

A structured interviewer-administered proforma will capture – Child: age, sex, developmental history, clinical diagnosis, schooling status; Parent/guardian: age, education, occupation, household socioeconomic indicators, and family history.(S1 Appendix)Clinical assessment will include vitals, anthropometry, general examination and documentation of Fragile X-associated clinical features using established checklists [5,12].

### Specimen collection and handling (dried blood spots)

Dried blood spots (DBS) will be collected on Quick Response (QR-coded) and labelled Whatman 903 Protein Saver Cards (Cytiva MA, USA) following standard DBS procedures, including universal precautions [13, 14] First, the finger will be pricked using a sterile lancet after alcohol cleansing. Then, blood will be applied to card circles; air dried horizontally for ~3 hours and each card stored in an individual pouch with a desiccant; labelled using QR-coded identification only and stored for a short term in a refrigerator at 2–8°C at zonal sites before batch transport. Samples will then be transported in batches using a dedicated medical courier service that complies with applicable biospecimen transport requirements to the coordinating molecular laboratory in Nnamdi Azikiwe University, Anambra State, Nigeria.

### Laboratory workflow

#### DNA extraction and quality assessment.

Genomic DNA will be extracted from dried blood spot (DBS) specimens at the coordinating molecular laboratory using a validated DNA extraction workflow optimised for *FMR1* molecular analysis and performed according to established standard operating procedures. The workflow includes specimen receipt and verification, DNA extraction, DNA quantification using a validated fluorometric method, and quality assessment to ensure adequate DNA yield and quality for long-range PCR before amplification. Samples with inadequate DNA yield or quality, or those that fail initial amplification, will undergo repeat extraction and repeat testing where sufficient specimen is available. As part of external quality assurance, a subset of samples will undergo repeat testing at the University of California, Davis molecular laboratory (UCD) to verify the accuracy and reproducibility of the molecular analyses [15].

#### Long-range PCR for FMR1 CGG-repeat region.

Long-range PCR will target the *FMR1* 5′UTR CGG repeat using established primer strategies described in Fragile X molecular workflows [13,15,16]. Amplification will be performed using Expand Long Template PCR System (Roche Diagnostics) or equivalent long-range, GC-rich buffer master-mix polymerase conditions, consistent with published Fragile X mutation detection methods and GC-enhancer use (e.g., betaine) for this locus [17–19]. Each run will include a No-template control (NTC) and Positive control DNA with known CGG repeat sizes (sourced/verified through established Fragile X reference laboratories, such as the UCD Molecular Laboratory, Sacramento under the direction of [name]) PCR products will be checked by agarose gel electrophoresis consistent with long-range Fragile X assays [17].

#### Amplicon purification and library preparation.

Successful amplicons will be purified (magnetic beads). Purified products will be quality-checked for concentration/integrity and library preparation done using the manufacturer-recommended required input appropriate for the amplicon size [20].

#### Nanopore sequencing and bioinformatics.

Amplicons will be prepared using Oxford Nanopore ligation sequencing chemistry with native barcoding, sequenced on R10.4.1 MinION Mk1D flow cells following Oxford Nanopore Technologies (ONT) guidance [21,22]. Reads will be aligned to a human reference genome using an established long-read aligner. *FMR1*-aligned reads will be analysed using long-read repeat tools to estimate per-read CGG repeat counts and mosaicism where present [23]. Alleles will be classified using internationally accepted thresholds (normal, intermediate, premutation, full mutation) as summarised in GeneReviews for *FMR1* disorders [24]. (S2 Appendix)

### Outcomes

The primary outcome is the proportion of participants with *FMR1* full mutation and/or premutation (those who test positive from the screening) in the selected cohort. Secondary outcomes include the distribution of CGG repeat sizes; the association of FMR1 expansion status with sociodemographic and clinical variables; the proportion of screen-positive families receiving counselling, referrals, and linkage to supportive interventions relevant to child mental health and developmental wellbeing; uptake of cascade testing offers; and building research capacity through mentoring early-career faculty members towards training in public health genetics. The study findings will be reported in accordance with the Strengthening the Reporting of Observational Studies in Epidemiology (STROBE) Statement.

### Data management and confidentiality

Participants will be assigned unique study IDs-QR codes; no names will appear on lab tubes/cards. Hard-copy records will be stored in locked cabinets, and electronic data will be housed in password-secured databases with role-based access. Identifiable and genetic data will be stored in password-protected databases with restricted access to authorised study personnel. Data transfers will be conducted using encrypted devices or secure electronic transfer systems in accordance with institutional data protection policies. Only authorised study personnel will access identifiable data.

### Statistical analysis plan

Data will be analysed using STATA version 16 (StataCorp LLC, College Station, TX, USA). Descriptive statistics will be performed using means/Standard deviation or medians/Inter-quartile range for continuous variables. Frequencies/percentages will be calculated for categorical variables. Prevalence estimates will be at 95% confidence intervals while Chi-square or Fisher’s exact tests used for categorical variables where appropriate to test for associations. Logistic regression analyses will be performed to identify factors associated with Fragile X positivity if the number of positive cases is sufficient to support reliable multivariable modelling. Where the number of positive cases is insufficient, analyses will be limited to descriptive and bivariate methods.

Statistical significance will be set at p < 0.05.

We will minimise potential sources of bias through recruitment across Nigeria’s six geopolitical zones, standardised eligibility criteria and data collection procedures, centralised laboratory analysis using validated protocols, and prespecified statistical analyses.

## Result disclosure, counselling, and follow-up

As part of the research protocol, parents, legal guardians or caregivers of children diagnosed with Fragile X syndrome through the study will receive the test results through post-test genetic counselling. Families will be counselled on the implications of the diagnosis and, where appropriate, reproductive counselling will be provided for carriers. Participants will be referred to the trained paediatric neurologists at the participating centres for appropriate clinical evaluation, follow-up and routine management, with referral to the coordinating centre at Nnamdi Azikiwe University Teaching Hospital (NAUTH) where specialist input is required. Referral to appropriate specialists and supportive therapies will also be done as appropriate. Any treatment, including consideration of targeted therapies such as metformin where clinically indicated, will be provided as part of routine clinical care and is outside the scope of this research protocol.

Evidence on treatment approaches, including metformin has been discussed in the Fragile X treatment literature; however, CHAMP-FX is not designed as a randomised treatment trial [25,26]. Relatives of participants who test positive will have cascade testing for relatives (where feasible).

The methodology for developing the integration model will involve stakeholder engagement with the Child Neurology Society of Nigeria, the Paediatric Association of Nigeria, the Federal Ministry of Health, selected State Ministries of Health, the National Primary Health Care Development Agency, and other relevant stakeholders from the public and private health sectors. Findings from the study will be presented to stakeholders and discussed to identify practical approaches for integrating Fragile X screening into existing paediatric and developmental health services in Nigeria. Data generated from the study, together with recommendations from the stakeholder engagement, will be synthesised to develop a context-appropriate Fragile X screening integration model for Nigeria.

### Ethical considerations

Ethical approval was obtained from the National Health Research Ethics Committee of Nigeria (NHREC)-NHREC Approval Number NHREC/01/01/2007-07/04/2025, and concordance from participating institutions. Written informed consent will be obtained from parents or legal guardians, and assent, where feasible, will be sought from children aged seven years and above using age-appropriate explanations, recognising the special needs of children with autism, intellectual disability, or developmental delay. To ensure understanding and ethical inclusivity, consent documents and data collection tools will be translated and administered by trained zonal coordinators in the locally relevant languages, with verbal explanations provided in participants’ preferred language where required.

All procedures will comply with NHREC guidelines and the Declaration of Helsinki [27]. Data and samples will be de-identified, securely stored, and accessible only to authorised research personnel. Confidentiality will be maintained throughout the study and dissemination.

The principles of voluntarism, beneficence, non-maleficence, confidentiality, and veracity will be strictly upheld. Participation is entirely voluntary, with the right to withdraw at any time without affecting access to care. Risks are minimal, limited to brief discomfort during specimen collection. Potential benefits include improved understanding of the causes of neurodevelopmental conditions and access to appropriate counselling and interventions where indicated. Participation will attract no additional cost and no financial inducement; only approved transportation reimbursement will be provided. All reporting and dissemination will be truthful and transparent.

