## Introduction

Neurodevelopmental disorders such as intellectual disability, global developmental delay, and autism significantly contribute to lifelong disability and mental health challenges globally [1].

Fragile X syndrome (FXS) is the leading inherited cause of intellectual disability and a major single-gene contributor to autism, resulting from cytosine-guanine-guanine (CGG) trinucleotide repeat expansion (>200 repeats) in the 5′ untranslated region (5’UTR) of the fragile X mental retardation 1 (*FMR1)* gene, resulting in gene silencing and reduced/absent fragile X mental retardation protein (FMRP) and subsequent synaptic dysfunction [2–4].

Beyond full mutation FXS, individuals carrying *FMR1* premutation alleles (approximately 55–200 CGG repeats) are at risk of Fragile X–associated premutation conditions, including Fragile X–associated primary ovarian insufficiency (FXPOI), Fragile X–associated tremor/ataxia syndrome (FXTAS), and Fragile X–associated neuropsychiatric disorders (FXAND), thereby extending the clinical and psychosocial burden of *FMR1*-related disorders also known as Fragile X disorders across the lifespan [4,5].

There have been significant global advances in diagnosis and targeted supports, in Nigeria, Fragile X disorders are rarely identified in routine clinical practice, mainly due to low awareness, limited access to molecular diagnostics, and persistent sociocultural stigma surrounding neurodevelopmental conditions [1,5–7] This implies that affected children and families experience delays in management, while policymakers and clinicians lack the data required for informed service planning.

The World Health Organisation has emphasised early identification and intervention for developmental challenges in low and middle-income countries (LMICs) and highlighted neglected needs of children with developmental disabilities [8]. CHAMP-FX aligns with these priorities and conducts a multi-site screening approach in high-risk paediatric populations, thereby strengthening local capacity for Fragile X testing and follow-up.

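### The risk statement confines risk to the blood sampling, although the protocol returns genetic results with consequences for carriers and relatives

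*Protocol article*

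**What the plan says.** Under Ethical considerations, the protocol article gives one sentence on risk: "Risks are minimal, limited to brief discomfort during specimen collection". No other risk is named there. The sentence that follows counts consequences of the result as benefits, namely a better understanding of what causes the child's condition and access to counselling and interventions. The same paragraph commits the study to veracity.

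Other sections describe what the test produces:

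- **Outcomes:** a positive screen is defined as "full mutation and/or premutation (those who test positive from the screening) in the selected cohort", so premutation carriers are among the positives.
- **Introduction:** premutation carriers "are at risk of Fragile X–associated premutation conditions". Those listed are ovarian insufficiency, a tremor/ataxia syndrome and neuropsychiatric disorders.
- **Result disclosure, counselling, and follow-up:** "where appropriate, reproductive counselling will be provided for carriers", and "Relatives of participants who test positive will have cascade testing for relatives (where feasible").
- **Data management and confidentiality:** identifiable and genetic data are held, with restricted access.
- **Discussion:** transmission risk from female carriers is put at 50%, and a shortage of genetic counselling and follow-up capacity is anticipated.

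**The concern.** The words that confine risk to the sampling do more than leave something out. They assert that nothing else is a risk. A short article may leave detail to a fuller protocol or to the consent form, but a closed list that omits the consequences of the test itself is a misstatement.

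What is at stake is participant protection. A finger prick carries little risk. A genetic result can tell a family that a child is a carrier, that a parent or sibling may be one too, and that conditions may appear later in life. An existing diagnosis of autism, intellectual disability or developmental delay discloses none of this. If the consent and assent forms were drafted from this sentence, families would agree to testing without having been told of these consequences.

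**Working it through.** The point rests on comparing sections; the protocol has no figure to reproduce for it.

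**Step 1. Compare the closed list with what the study does.**

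| Consequence of taking part | Where the protocol describes it | Covered by the risk sentence? |
|---|---|---|
| Discomfort at the finger prick | Specimen collection and handling | Yes |
| Learning that the child has a premutation, with later-life conditions attached | Outcomes; Introduction | No |
| Carrier status and its reproductive implications | Result disclosure; Discussion (50% transmission from female carriers) | No |
| Implications for relatives through cascade testing | Result disclosure; Outcomes (uptake is a secondary outcome) | No |
| Holding of identifiable genetic data | Data management and confidentiality | No |
| Disclosure where counselling capacity is short | Discussion | No |

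The study's own test or data handling creates each of the last five rows. None was present before enrolment.

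**Step 2. Check the paragraph against itself.** It counts effects of the result as benefits of participation. If what follows from a result belongs on the benefit side, it cannot be left off the risk side. The safeguards described elsewhere (post-test counselling, coded identifiers, restricted access, referral) also presuppose risks that the sentence excludes.

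**Step 3. Is a positive result foreseeable?** Inputs from Sample size and allocation: planning prevalence P = 0.023 and n = 102 (6 zones × 17).

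- Expected positives: n × P = 102 × 0.023 = 2.35.
- Chance of at least one: 1 − (1 − P)^n = 1 − 0.977^102 = 0.907.

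The protocol does not say whether 0.023 includes premutations, so a range is assumed:

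| Assumed prevalence | Expected positives | Chance of at least one |
|---|---|---|
| 1% | 1.0 | 0.64 |
| 2.3% | 2.3 | 0.91 |
| 5% | 5.1 | 0.995 |

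Across the range, at least one positive disclosure is more likely than not. These figures show scale only; the conflict in Step 1 does not depend on them.

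**The case against.** The strongest reply is that the sentence stands in a journal article and not in a consent form. The forms are not shown. The ethics section describes translated consent documents with verbal explanation, and the section on patient and public involvement says that information materials will be refined with parents. A reader might infer that families actually consent on this sentence, but the documents do not establish that. The reply stands to that extent, and the point is limited accordingly. It does not make the protocol sentence correct.

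The second reply concerns the Introduction. Its reference to "persistent sociocultural stigma surrounding neurodevelopmental conditions" explains why Fragile X disorders are rarely identified, and every enrolled child already has a neurodevelopmental diagnosis. The phrase "thereby extending the clinical and psychosocial burden of" describes the FMR1-related disorders and not the test. A reader might conclude that the protocol itself names the result as the main source of risk. It does not: no section ranks risks or calls disclosure one. Both passages are background only. The conflict rests on carrier status, relatives, later-life conditions, stored genetic data and limited counselling capacity.

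The third reply is that protections are planned and national ethics approval was obtained. Both are true. They leave little more than a wording change, but neither reconciles the sentence with the other sections.

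Finally, a reader might infer damage to the secondary outcomes. With 2 or 3 positive families, one refusal moves a family-level proportion by 1/2 = 50 or 1/3 = 33 percentage points. That follows from the small denominator whatever the reason for refusal. Nothing in the protocol shows that families surprised by a result would decline counselling or cascade testing.

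**Conclusion.** The concern holds as a misstatement in the ethics section. A sentence that confines risk to the sampling cannot stand beside the protocol's plans to disclose FMR1 results, treat a premutation as positive, counsel carriers, test relatives and keep identifiable genetic data while counselling capacity is short.

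The statement describes the risk for all 102 planned participants. About 2.3 of them are expected to be positive at the planning prevalence, or 1.0 to 5.1 over an assumed 1% to 5%. Whether any family is misinformed depends on the consent and assent forms, which are not shown. Sample size, statistical analysis and the primary outcome are not affected, and no effect on the linkage or cascade-uptake proportions is shown. The change is worth making because it concerns participant protection and costs little.

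**What to change.** Reword the risk sentence under Ethical considerations in two parts. The first part states that the physical risk of sampling is minimal. The second names the risks of a genetic result:

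- informational and psychosocial: distress, stigma, and learning of conditions that may appear later in life;
- familial: implications for parents, siblings and reproductive decisions;
- privacy: identifiable genetic data are held.

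Next to these, name the safeguards already in the protocol: post-test genetic counselling, coded identifiers, restricted access and referral. Then check that the consent and assent forms, in every language used, say the same, and correct them where they do not.

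The cost is a text change, a notification to the ethics committee, a slightly longer consent discussion and possibly a few refusals. No procedure, sample size or analysis changes.
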